## Ethical considerations

The present study project will be conducted according to the ethical conducts established in Resolution 466/2012, of the National Health Council. The participants will have their copy of the TCLE, which will be clarified by a member of the team of researchers, before the beginning of any procedure in the study. The project will be conducted after approval by the Ethics Committee to which the project will be assigned through the Plataforma Brasil.

During the intervention period, if any osteomuscular pain or discomfort or malaise is reported during the training, it will be stopped immediately. If there is a need for care or procedure that is beyond the competencies of the researcher, they can be performed by the nursing service of the Clinical Research Center ([name]) or even by the Emergency Service of the institution. In this case, the researcher will contact him/her by [name] and request contact with the regulating doctor, explain the situation and accompany the patient to the Emergency. The individual will be moved by wheelchair, stretcher or ambulance. In addition, the researchers responsible will contact a relative or close person (reported by the participant in the first visit), to inform about what happened.

## Statistical analysis

Shapiro-Wilk and Levene tests will be used for data normality and variance homogeneity, respectively. If the data present normal and homogeneous distribution, parametric statistics will be used. Transformations will be performed if the data do not present normal distribution to make them parametric. The Generalized Estimating Equations (GEE) and the Bonferroni post-hoc test will be used for the comparison between the moments and groups/ interventions. In addition, statistical analysis by protocol will be performed, in which those who have presented three consecutive absences in training will be excluded from the analysis, as well as those who obtain a frequency lower than 75% during the period of interventions. Statistical analysis by intention to treat will also be performed, in which all randomized participants will be included in the analyses. The level of significance adopted will be α = 0.05 for all analyses. The statistical package SPSS version 22.0 will be used to perform the statistical procedures.

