### Specific Objectives

To evaluate and compare the effects of 12 weeks of combined training with different weekly frequencies on the following outcomes in middle-aged and older individuals with hypertension:

*Primary outcomes*

- Daytime, nighttime and 24-hour systolic and diastolic BP, evaluated through ambulatory BP monitoring (ABPM);

- Glycosylated hemoglobin (HbA1c), evaluated through blood collection using the high performance liquid chromatography method.

*Secondary outcomes*

- Endothelial function, evaluated by ultrasonography.

- Cardiorespiratory fitness, evaluated through an ergoespirometric test of maximum effort.

- Neuromuscular function, evaluated through chair-stand test, isometric handgrip test, vertical jump, medicine ball throw and balance tests;

- Quality of life, evaluated through the questionnaire WHOQOL-BREF.

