The sample will consist of 98 participants (49 in each intervention), who will be included according to the above criteria. The sample size calculation was performed considering a minimum difference of 4 mmHg, and dispersion (standard deviation) of ± 10 mmHg in systolic and diastolic BP. A statistical power of 80% and an alpha error of P<0.05 were adopted.

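### A preliminary normality test decides whether each primary outcome is transformed, so the scale of the primary BP contrast is not fixed in advance and may not be the mmHg difference used for sizing

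*Protocol*

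**What the plan says.** The Protocol's Statistical analysis section opens with two preliminary tests: "Shapiro-Wilk and Levene tests will be used for data normality and variance homogeneity, respectively". Parametric methods follow if both are satisfied. If normality fails, the instruction is: "Transformations will be performed if the data do not present normal distribution to make them parametric". The model comes next: "The Generalized Estimating Equations (GEE) and the Bonferroni post-hoc test will be used for the comparison between the moments and groups/ interventions". The significance level is 0.05 for all analyses, and both an intention-to-treat and a per-protocol analysis are planned.

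The section does not name a transformation. It does not say whether the test is applied to raw values, changes or residuals, or by arm, by moment or pooled. It mentions no back-transformation and no analysis kept on the original scale. It gives no link function or variance estimator for the GEE.

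Under Specific Objectives the primary outcomes are "Daytime, nighttime and 24-hour systolic and diastolic BP, evaluated through ambulatory BP monitoring (ABPM"), which makes six variables, plus HbA1c, so seven in all. Under Participants recruitment the trial is sized on an additive scale: "The sample size calculation was performed considering a minimum difference of 4 mmHg, and dispersion (standard deviation) of ± 10 mmHg in systolic and diastolic BP".

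**The concern.** A rule of the form test, then transform, lets the observed data choose the effect measure, outcome by outcome. Two consequences follow.

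First, the primary BP contrast may no longer be the quantity used for planning. With a log transformation it becomes a ratio of geometric means. With a square root or another power it is a difference on a scale with no clinical unit. In neither case is it directly the mmHg difference of the sample-size statement.

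Second, 24-hour, daytime and nighttime pressures describe the same physiology and will be read side by side. Tested separately, some could stay in mmHg while others move to another scale, through chance alone.

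The rule also buys little. GEE inference rests on a correct model for the mean and, with the usual sandwich variance, requires neither normal outcomes nor equal variances.

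**Working it through.** **Inputs from the Protocol.** Seven primary outcomes (Specific Objectives); 49 participants per arm, 4 mmHg difference, SD 10 mmHg (Participants recruitment); two arms and two moments, weeks 0 and 13 (Study Design, Evaluations); level 0.05 (Statistical analysis). **Assumptions.** Shapiro-Wilk is run at 0.05, and any rejection for an outcome triggers its transformation.

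**The plan's own figure.** The two-sample formula n = 2 × [SD × (z₀.₉₇₅ + z₀.₈₀)/difference]² gives 2 × [10 × (1.960 + 0.842)/4]² = 98.1, or 99 per arm after the small-sample correction, not 49. Without the factor 2 the formula gives 49.06. Change scores with a pre-post correlation of 0.75 also give 49.06, but no correlation is stated. That discrepancy is a separate matter. What counts here is that the design target is an additive difference in mmHg.

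**Chance of a needless transformation when data are truly normal, tests independent.**

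- One outcome, four arm-by-moment tests: 1 − 0.95⁴ = 1 − 0.8145 = 18.5%. Simulation at 49 per cell gave 18.4%.
- At least one of seven outcomes, one test each: 1 − 0.95⁷ = 1 − 0.6983 = 30.2%.
- At least one of seven outcomes, four tests each (28 tests): 1 − 0.95²⁸ = 1 − 0.2378 = 76.2%.

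**Effect of correlation (simulated, correlations assumed).**

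- Four tests per outcome, six BP variables equally correlated, HbA1c independent: about 73–75% at a BP correlation of 0.6, 71% at 0.8 and 61–62% at 0.9.
- Structured correlations (day-night 0.7–0.8, systolic-diastolic 0.6–0.7, pre-post 0.7–0.8, 24-hour pressure built from day and night): 65–68% with four tests per outcome, and about 24% with one pooled change-score test per outcome.

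The unstated testing unit moves the answer far more than the correlation does.

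**If there is mild real skewness** (0.5, assumed): a single test rejects in about 21% of samples of 49 and 43% of samples of 98. At least one of four cells of 49 rejects in 63%.

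**Is normality needed at this size?** A two-sample t-test at 49 per arm, simulated with the same skewed distribution in both arms, had type I error of 4.8%, 5.1% and 4.8% at skewness 0.5, 1 and 2. The transformation is not needed to protect the test.

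**What a log scale does to the target** (BP levels assumed): 4 mmHg is 4/120 = 3.3% at 120 mmHg and 4/150 = 2.7% at 150 mmHg. Conversely, a fixed ratio of 4/130 = 3.08% is 120 × 4/130 = 3.7 mmHg at 120 and 150 × 4/130 = 4.6 mmHg at 150. No single ratio corresponds to 4 mmHg.

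**The case against.** The strongest reply is that the practical effect may be small. Ambulatory BP averages are often near normal and would then usually stay untransformed. The analyst is blinded by group codes (Randomization and allocation concealment), and a transformation would apply to both arms alike, so the rule gives little scope to favour one arm. The 4 mmHg is a sample-size input, not a margin or success threshold, and nothing forbids reporting raw or back-transformed means as well. Details of the transformation could sit in a statistical analysis plan.

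Much of this stands, and it limits the point:

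- A reader might infer that the rule inflates type I error or biases the comparison. The documents do not support that; a GEE on a transformed scale can be a valid test of its own null hypothesis.
- A reader might take 76% as the risk. It is the top of a range and rests on a testing unit that the Protocol does not state.
- A reader might suppose that robust standard errors are already planned. The Protocol names only GEE and Bonferroni.
- A reader might expect the intention-to-treat and per-protocol sets to land on different scales. The Protocol does not say that the normality test is repeated by analysis set.
- The ratio interpretation applies to a log transformation only, and the mmHg argument applies to the six BP outcomes, not to HbA1c.

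What does not stand is the idea that this is merely detail left open. The Protocol itself states the rule, for all outcomes. Blinding limits biased choice but does not fix the scale beforehand, and optional reporting of mmHg means does not make them the pre-specified primary contrast.

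**Conclusion.** The point holds as a weakness of pre-specification and interpretability. As written, a Shapiro-Wilk result decides the scale of each primary contrast in a trial sized on an additive mmHg difference, and related BP outcomes could end on different scales. For truly normal outcomes, the chance of at least one needless transformation among the seven is about 30% (one test per outcome) to 76% (four per outcome) under independence, and about 24% and 61–75% respectively under the assumed correlations. All these figures assume testing at 0.05 with any rejection acting as a trigger. It should be corrected, but it does not by itself threaten the validity of the comparison between arms.

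**What to change.** Replace the test-then-transform rule with a fixed primary analysis: GEE with identity link on the original scale, BP in mmHg and HbA1c in percentage points, with robust (sandwich) standard errors stated explicitly, regardless of the Shapiro-Wilk or Levene results. Inspect residuals, and report any transformed or bootstrap analysis only as a sensitivity check. Name the scale of each secondary outcome in advance, since the present rule covers those too.

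The cost is a few sentences in the Statistical analysis section and no extra data. There is one small downside: some efficiency may be lost if an outcome is strongly skewed. HbA1c is the likeliest case, because the eligibility criteria exclude proliferative diabetic retinopathy but not diabetes as such. The sensitivity analysis would show whether it matters.

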## Evaluations

Before the study begins (week 0) and at the end of the intervention period (week 13), participants will perform evaluations regarding BP, glycated hemoglobin, endothelial function, fitness level, and quality of life. Divided into 3 visits with 24-72h intervals between visits, the different evaluations aim to verify the possible effects of the different interventions on the outcome variables of the study. A food record will be used to characterize eating behavior and to evaluate a possible interference of eating with training responses. The subjects will be recommended not to change their eating habits during the study period.

In the first visit, after signing the TCLE, an anamnesis will be performed to characterize the sample, collection of anthropometric measurements through measures of height and body mass, performed from a stadiometer and an analog balance scale (brand FILIZOLA, BRAZIL). With these values their body mass indexes (BMI) will be calculated, according to the equation mass (kg)/height(m)². A questionnaire will also be carried out to evaluate the quality of life of the participants (WHOQOL-BREF). Also in this session, BP measurements will be performed (after 20 minutes of rest) followed by a familiarization with the exercises that will be used in strength and muscle power tests and with the mask that will be used in gas collection during the cardiopulmonary test.

In the second visit, new BP measures will be performed and the endothelial function evaluation conducted through flow-mediated dilation analysis. The resting electrocardiogram and blood collection will also be performed for analysis of glycated hemoglobin levels. From this blood collection, a sample will be used for analysis of total cholesterol, HDL-c, LDL-c, VLDL-c, which will serve to characterize the sample. Afterwards, the ambulatory blood pressure monitoring equipment (ABPM) will be placed. After 24h of the second visit, each patient must return to the laboratory to remove the ABPM.

On the third visit, after ABPM removal, the evaluation of strength and muscle power tests will be conducted, as well as the cardiorespiratory and unipodal balance evaluation. First the strength, power and unipodal equilibrium tests will be conducted, and after a 10-minute rest, the cardiopulmonary test will be conducted.

*Blood pressure measurement*

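### The planned GEE comparison of moments and groups names no baseline adjustment, so the TC4–TC2 difference is estimated less precisely than the week-0 data allow; the size of the loss depends on a correlation that the protocol does not give

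*Protocol*

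**What the plan says.** The protocol's Statistical analysis section gives the comparison in one sentence: "The Generalized Estimating Equations (GEE) and the Bonferroni post-hoc test will be used for the comparison between the moments and groups/ interventions". It names no covariate. It also does not say whether the group-by-moment term or a pairwise week-13 test answers the primary question.

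The Evaluations section fixes the two moments: "Before the study begins (week 0) and at the end of the intervention period (week 13), participants will perform evaluations regarding BP, glycated hemoglobin". Each participant is therefore due one value before and one after the intervention. The primary outcomes under Specific Objectives are "Daytime, nighttime and 24-hour systolic and diastolic BP, evaluated through ambulatory BP monitoring (ABPM") and "Glycosylated hemoglobin (HbA1c), evaluated through blood collection using the high performance liquid chromatography method".

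The sample size under Participants recruitment is 98 participants, 49 per arm, "considering a minimum difference of 4 mmHg, and dispersion (standard deviation) of ± 10 mmHg in systolic and diastolic BP". It adds: "A statistical power of 80% and an alpha error of P<0.05 were adopted". No section states a correlation between week 0 and week 13, or says whether the SD of 10 belongs to single values or to changes. Randomisation is stratified by age group only.

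**The concern.** Randomisation makes the two arms equal in expectation at week 0. A model with a free week-0 mean in each arm does not use that knowledge. A change contrast subtracts the whole baseline difference, although only a fraction r of it carries through to week 13 on average. A week-13 contrast subtracts none of it. Either way, noise stays in the estimate that a baseline-adjusted analysis removes.

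Precision on the primary between-arm question is at stake. Neither blood pressure nor HbA1c is a stratification factor, so chance differences at week 0 are not limited by design. The planned 49 per arm also leave little to spare for a 4 mmHg difference.

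**Working it through.** **Inputs.** From the protocol: 49 per arm, difference 4 mmHg, SD 10 mmHg, 80% power, alpha 0.05. Assumed: two-sided test, normal approximation, equal variances at both times, complete data, no multiplicity correction, and r varied from 0.3 to 0.9 because the protocol gives none.

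**The plan's own figure.** The two-arm formula gives n per arm = 2 × [10 × (1.960 + 0.842)/4]² = 98.1, so 99 per arm and 198 in total. The stated 98 in total is not reproduced. The one-sample or paired formula, without the factor 2, gives 49.06. With 49 per arm and a working SD of 10, power is 51%. That is a separate sample-size point; here it only shows that precision is scarce.

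**Variances of the TC4–TC2 difference (n = 49 per arm).**

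- Week-13 contrast: (2/n) × SD²
- Change contrast: (2/n) × 2 × SD² × (1−r)
- Baseline-adjusted: (2/n) × SD² × (1−r²)

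Adjusted over change is (1−r²)/[2(1−r)] = (1+r)/2, so the loss is (1−r)/2. Adjusted over week-13 is 1−r², so the loss is r².

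**SD 10 read as the SD of single values.** The standard error is the square root of the variance. At r = 0.5 it falls from 2.02 (change) to 1.75 (adjusted); at r = 0.7 from 1.56 to 1.44.

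| r | Loss v change, (1−r)/2 | Loss v week 13, r² | Power, change | Power, adjusted |
|---|---|---|---|---|
| 0.3 | 35% | 9% | 38.7% | 54.6% |
| 0.5 | 25% | 25% | 50.8% | 62.8% |
| 0.6 | 20% | 36% | 60.0% | 69.7% |
| 0.7 | 15% | 49% | 72.4% | 79.2% |
| 0.8 | 10% | 64% | 87.9% | 91.0% |
| 0.9 | 5% | 81% | 99.3% | 99.5% |

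The week-13 contrast has 50.8% power at every r. The number per arm for 80% power falls from 99 (change) to 74 (adjusted) at r = 0.5, and from 59 to 51 at r = 0.7.

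**SD 10 read as the SD of changes.** The change contrast then has 50.8% power at every r. The SD for the adjusted analysis is 10 × √[(1+r)/2]. Power rises to 62.8% at r = 0.5 and to 57.4% at r = 0.7.

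**Check by simulation** (4,000 trials, 49 per arm, true difference 4 mmHg). The variance ratio, adjusted to change, was 0.758 at r = 0.5 (theory 0.75) and 0.850 at r = 0.7 (theory 0.85). In five data sets at each r, the group-by-moment estimate of a fitted GEE equalled the difference in mean changes to six decimals.

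**The case against.** The strongest reply is that the protocol is silent on covariates and does not exclude them. GEE accepts a baseline covariate or a common week-0 mean, and such terms are often left to a SAP, which is not at hand. This stands in part: the choice of GEE is not the fault, and nothing in the text forbids adjustment. But the section does go beyond naming a method. It sets the comparison as one between moments and groups, with week 0 as one of the moments. Read as written, that is an unadjusted comparison, and a better one exists with the same data.

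Four stronger readings are tempting, and the documents support none of them.

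- **A fixed loss of 15–25%.** A reader might infer this, but it holds only for r from 0.7 to 0.5, equal variances and the change contrast. One r need not fit both ambulatory blood pressure and HbA1c.
- **Week 0 is ignored.** It is in the model as a response. What is given up is the knowledge that the arms share a week-0 mean.
- **The estimate is biased.** Across randomisations the unadjusted contrasts are unbiased. A chance baseline imbalance affects the estimate in a particular trial, and adjustment removes that noise.
- **A mixed population makes the loss larger.** Treated and untreated hypertension are both admitted, and diabetes is not itself an exclusion. Stable differences between people raise r, which shrinks the loss against a change contrast.

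A further objection concerns the remedy. Regressing week 13 on arm and week 0 drops anyone without a week-13 value, whereas the intention-to-treat analysis is meant to include all randomised participants. It also does not report within-arm change, which the objectives ask for. Both objections are fair, and they decide which remedy should come first.

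**Conclusion.** The point holds as one of efficiency. For any r between 0 and 1, both contrasts that the text allows are less precise than a baseline-adjusted one. The direction does not depend on the missing inputs, apart from a negligible cost of estimating one slope with 98 participants. The size does depend on them. Against the change contrast the loss is moderate at r of about 0.5 and slight at 0.9. Against the week-13 contrast it grows with r. In power for 4 mmHg, the gain over the change contrast is about 12 points at r = 0.5 on either reading of the SD. At r = 0.7 it is about 7 points on either reading: 72% to 79% if the SD is that of single values, 51% to 57% if it is that of changes. These figures rest on equal variances, complete data and a two-sided 0.05 test. The change is worth making, but the stated analysis is not invalid without it.

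**What to change.** Keep the GEE or repeated-measures framework, but specify one common week-0 mean for both arms and separate week-13 means. The within-person correlation must be estimated: under an independence working correlation, this model returns the plain week-13 difference and the gain is lost. The model keeps every randomised participant with a week-0 value and still reports within-arm change. Alternatively, for participants with week-13 data, regress the week-13 value on arm and the week-0 value of the same outcome.

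In either case, name the baseline-adjusted TC4–TC2 difference at week 13, with its 95% CI, as the primary between-arm result. That also settles which contrast answers the primary question. State whether the SD of 10 is that of single values or of changes, and which r is assumed.

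The cost is wording and a little more model specification; no new data or visits are needed. If r proves high, the gain over a change contrast will be small.

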## Training programs

The TC2 and TC4 groups will perform the training with progressive intensity and volume, and will perform the same weekly training overload (i.e., minutes per week, series, repetitions, relative intensity and exercises), but will have this overload divided into different weekly frequencies. The training will last 12 weeks, with a total weekly volume of 120 min in the first weeks (weeks 1-6), progressing to 150 min/week in the last weeks (weeks 7-12). Therefore, the groups will differentiate their training exclusively by the number of weekly sessions that will be used to perform this training, with one group performing 2 weekly sessions and the other group 4 weekly sessions.

The first part of the session will consist of the following RE: push-up, squat, unipodal balance, inverted row, calf raise and crunch. The progression in volume will be performed by increasing the number of sets and repetitions. The intensity of the effort will be adjusted from the range of movement of the exercises, speed of execution, and variations in the number of supports to stabilize the exercises. Individuals must perform 1-4 series of 10-15 repetitions with the load corresponding to 60-70% of 1RM monitored through rating of perceived exertion (RPE), monitored through the CR10 scale. An interval of 90-120 seconds will be adopted between sets and exercises. The second part of the session will consist of AE performed on a treadmill or track and will last 20-50 minutes. The intensity of these sessions will be controlled through the heart rate reserve (HR _reserve_) of the individuals, using intensities between 60-70% of HR _reserve_. In the absence of HR monitors, the stress perception scale corresponding to the above intensities will be used, monitored through the BORG scale with rates of 6-20. In the last session of the week at each 4-week period, after the RE and at the end of each session, information will be recorded regarding the RPE of the participants in the session and the level of enjoyment when conducting the training. It should be noted that the training sessions will always start with the RE, and later on, they will perform the AE, as this seems to be the best order to conduct the training in this population[^41^](#_ENREF_41)^,^ [^42^](#_ENREF_42).

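### The per-protocol rule counts consecutive missed sessions, so a one-week gap removes a four-session participant but keeps a two-session participant

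*Protocol*

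**What the plan says.** The Statistical analysis section of the protocol defines two analysis sets. The per-protocol set is introduced with "In addition, statistical analysis by protocol will be performed" and has two exclusion criteria. The first is that "those who have presented three consecutive absences in training will be excluded from the analysis". The second follows directly: "as well as those who obtain a frequency lower than 75% during the period of interventions". The section then adds: "Statistical analysis by intention to treat will also be performed, in which all randomized participants will be included in the analyses".

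The Training programs section fixes the schedule: "The training will last 12 weeks", "with one group performing 2 weekly sessions and the other group 4 weekly sessions". It also says that the two groups "will perform the same weekly training overload", so weekly volume is meant to be equal and only the number of sessions differs. That volume is 120 minutes a week in weeks 1 to 6 and 150 in weeks 7 to 12.

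The arms are called CT2 and CT4 in the Abstract and TC2 and TC4 in the Methods. CT2 and CT4 are used here.

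**The concern.** The consecutive-absence criterion is a fixed count of three, applied to arms that differ by design in how many sessions fill a week. The same interruption therefore yields twice as many absences in CT4 as in CT2. Any per-protocol set selects on behaviour after randomisation. This one also sets the threshold at a different length of interruption in each arm, and what moves the threshold is session frequency, the factor under study.

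Short interruptions come from illness, travel or loss of motivation, and these may be related to blood pressure, HbA1c or fitness. If so, the per-protocol comparison sets a CT4 group cleared of people with a one-week gap against a CT2 group that still contains them. A difference between the arms, or the lack of one, could then partly reflect who was removed. The protocol does not allow the direction of that bias to be predicted.

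**Working it through.** The protocol states no expected number of per-protocol exclusions, so there is no figure of its own to reproduce.

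**Inputs from the protocol**
- Duration 12 weeks; 2 or 4 sessions a week; equal weekly volume (Training programs).
- Exclusion after three absences in a row, or for attendance below 75% (Statistical analysis).
- 49 participants per arm (Participants recruitment), used only to turn percentages into people.

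**Step 1. Planned sessions.** CT2: 12 × 2 = 24. CT4: 12 × 4 = 48.

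**Step 2. What three consecutive absences mean**

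| | CT2 | CT4 |
|---|---|---|
| Weeks of training | 3/2 = 1.5 | 3/4 = 0.75 |
| Share of sessions | 3/24 = 12.5% | 3/48 = 6.25% |
| Attendance if nothing else is missed | 21/24 = 87.5% | 45/48 = 93.8% |

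**Step 3. One week away.** On a fixed weekly schedule, a seven-day gap covers 2 sessions in CT2 and 4 in CT4. Attendance is 22/24 = 91.7% and 44/48 = 91.7%. Two is below three, so the CT2 participant stays. Four is not, so the CT4 participant is excluded. Both have lost one week of the same weekly volume. This step needs no assumption about absence rates.

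**Step 4. The 75% rule for comparison.** It allows 24 − 18 = 6 missed sessions in CT2 and 48 − 36 = 12 in CT4, which is three weeks in either arm. It scales with the schedule.

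**Step 5. How many would be excluded.** The protocol gives neither a rate nor a pattern of absence, so two assumed patterns are shown.

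*(a) Scattered misses.* Each session is missed independently with probability p. Let P(n) be the probability of no run of three misses in n sessions. Then P(0) = P(1) = P(2) = 1 and P(n) = (1 − p)[P(n−1) + p·P(n−2) + p²·P(n−3)]. The run rule excludes 1 − P(24) of CT2 and 1 − P(48) of CT4. The columns for both rules also remove anyone with more than 6 of 24 or 12 of 48 sessions missed.

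| p | Run rule, CT4 | Run rule, CT2 | Both rules, CT4 | Both rules, CT2 |
|---|---|---|---|---|
| 5% | 0.6% | 0.3% | 0.6% | 0.3% |
| 10% | 4.1% | 2.0% | 4.1% | 2.5% |
| 15% | 12.5% | 6.2% | 13.5% | 9.8% |
| 20% | 26.1% | 13.5% | 32.0% | 24.7% |

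*(b) Whole-week absences.* Each week is missed entirely with probability w, independently of other weeks. One missed week is enough for exclusion in CT4, so the share is 1 − (1 − w)^12. At w = 2% this is 1 − 0.98^12 = 21.5%. CT2 needs two missed weeks in a row. With R(n) the probability of no such pair in n weeks, R(0) = R(1) = 1 and R(n) = (1 − w)[R(n−1) + w·R(n−2)], and the share is 1 − R(12).

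| w | Run rule, CT4 | Run rule, CT2 |
|---|---|---|
| 2% | 21.5% | 0.4% |
| 5% | 46.0% | 2.6% |
| 10% | 71.8% | 9.7% |

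**Step 6. In people, of 49 per arm.** Scattered misses at 10%, both rules: 0.041 × 49 = 2.0 in CT4 and 0.025 × 49 = 1.2 in CT2. Whole-week absences at 2%, run rule: 0.215 × 49 = 10.5 in CT4 and 0.004 × 49 = 0.2 in CT2.

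The run rule excludes more of CT4 in every case tried. The gap ranges from less than one person to a large imbalance.

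**The case against.** The strongest reply is that the fault touches only one of two stated analyses. The intention-to-treat analysis includes everyone randomised, and no attendance rule enters it. That stands, and it limits the seriousness of the point.

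It can also be said that the large percentages come from assuming that absences arrive as whole weeks, the pattern that most separates the arms. That stands too. Under scattered misses the difference is modest. The direction is established; the size is not.

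A third reply is that the rule never uses the word sessions. But training is delivered in sessions and no other unit is offered, so a missed session is the plain reading. If weeks or days were meant, the text needs to say so.

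A reader might infer more than the protocol supports:

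- *That CT4 keeps only near-perfect attenders.* It does not. A CT4 participant who misses one session every week attends 36/48 = 75%, which is not below 75%. If those misses are never three in a row, the participant is retained. The rule removes people with a short continuous gap, not people with low attendance.
- *That the two exclusion criteria contradict each other*, because someone at 45/48 is removed. They are separate criteria joined as alternatives, one for a continuous gap and one for total attendance. The run rule equally removes a CT2 participant at 21/24 = 87.5%.
- *That the conclusion can be picked afterwards because intention to treat is not called primary.* Ranking the analysis sets is commonly left to a statistical analysis plan, which may exist and is not shown. The protocol already commits to an intention-to-treat analysis.
- *That attendance logs would unblind the statistician.* The randomisation section blinds the analyst of the outcome variables by coded groups. Nothing says that this person handles the logs or sets the per-protocol flag.

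**Conclusion.** The point holds for the per-protocol analysis and should be fixed, but it does not threaten the trial's all-randomised comparison. The part that needs no assumption about absence rates is that equal one-week gaps, at equal 91.7% attendance and equal lost volume, lead to exclusion in CT4 and retention in CT2. It rests only on reading an absence as a missed session and on a regular weekly schedule.

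The resulting imbalance depends on how people miss training, which the protocol does not forecast. A fair statement of the range is from about 4.1% against 2.5% excluded (10% scattered misses, both rules) to about 21.5% against 0.4% (whole weeks missed at 2% per week, run rule). Whether this biases the estimated effect also depends on how far interruptions are related to the outcomes, and that is unknown.

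**What to change.** In the Statistical analysis section, restate the consecutive-absence criterion in a unit that means the same in both arms: either one length of calendar time without training or one amount of missed weekly training volume. Alternatively, remove it and rely on the 75% attendance rule, which already scales with planned sessions. Either change takes a sentence and leaves the training programme, the data collected and the intention-to-treat analysis as they are. It should be settled before attendance by arm is examined.

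The cost is that the per-protocol set will keep some participants with a short break in training. The 75% rule alone would not make exclusion rates exactly equal either: under scattered misses of 10% it removes 0.75% of CT2 and 0.07% of CT4, because chance variation is larger over 24 sessions than over 48. It does put the limit at the same three weeks of missed training in both arms.
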